### Objectives

The main objectives of study 1 (scale and questionnaire development) are as follows:

To develop psychometrically valid scales to assess women’s knowledge of cervical cancer and attitudes, beliefs, and knowledge about HPV testing and self-sampling.To evaluate the feasibility and acceptability of using a web-based survey related to Canadian women’s knowledge, attitudes, beliefs, and preferences about new HPV testing–based cervical cancer screening programs.

The main objectives of study 2 (expanded population-based survey of Canadian women) are as follows:

To estimate differences in HPV and cervical cancer screening knowledge and attitudes, beliefs, and preferences regarding HPV testing between women who are adequately screened and those who are underscreened.To estimate the multivariable associations between psychosocial factors (eg, knowledge, attitudes, beliefs, and sociodemographics) and intentions to use HPV testing and self-sampling in women who are adequately screened and those who are underscreened.

## Study 1: Questionnaire Development and Scale Validation

### Methods

#### Study 1: Ethics Approval

Study 1 received approval from the Research Ethics Board of the Centre intégré universitaire de santé et de services sociaux (the Integrated Health and Social Services University Network) of West-Central Montreal (project ID 2021-2632) in March 2021.

#### Theoretical Frameworks

Questionnaire development and item selection for the development of the scales were guided by relevant theoretical frameworks. The selection of psychosocial factors influencing intentions to engage in HPV testing was informed by 2 theories: the Theory of Planned Behavior (TPB), which suggests that attitudes, beliefs, subjective norms, and perceived behavioral control influence intentions and subsequent health behaviors [53], and the Health Belief Model (HBM), which posits that the likelihood of behavior change is influenced by perceived susceptibility, seriousness and threat of the disease, perceived benefits of adopting protective health behaviors (ie, screening), cues to action (eg, information and social influence), sociodemographics, and knowledge [54].

#### Study Design

To build robust measures, we followed a rigorous stepwise process involving review of the scientific literature, discussions, and consensus development with our experienced team of researchers and consultation with project collaborators and the population of interest. This process is described chronologically, separated into 3 steps: phase 1A—questionnaire development, phase 1B—questionnaire validation, and phase 1C—survey testing and psychometric validation. As of May 2022, phases 1A and 1B are completed, and data analysis is ongoing for phase 1C.

#### Phase 1A: Questionnaire Development

##### Literature Search

We reviewed the literature for existing relevant scales using a validated and updated search strategy that we used for a recently published knowledge synthesis summarizing factors associated with HPV test acceptability in primary screening for cervical cancer [24]. Embase, Global Health, PsycINFO, MEDLINE, and CINAHL databases were searched from January 2017 to October 2019. After removing duplicates, a total of 1477 references were screened by title and abstract, and 89 full-text articles were reviewed to identify relevant scales. Our team found and reviewed 13 scales (including 4 scales that were identified in past literature searches [44,45,48-50,55-62]). Our overall conclusions indicated that existing questionnaires were incomplete in the following ways: not including questions about HPV testing in cervical cancer screening (eg, only including items related to the Pap test), having inadequate psychometric validation analyses (eg, no factor analysis, only partial factor analysis with exploratory factor analysis [EFA], or no reliability testing at all), having inadequate psychometric properties (eg, internal consistency <0.6), being unsuitable for our study design (eg, being designed to administer verbally), and having limited sampling characteristics (eg, only adolescents or in a specific culture or context). Nevertheless, many individual items were potentially relevant to our objectives.

##### Item Selection

To evaluate potentially relevant items together and guide their selection, a large pool of items (n=781) was created, and a questionnaire structure was drafted (Figure 1) with 4 potential scales: cervical cancer knowledge, HPV testing knowledge, HPV testing attitudes and beliefs, and HPV self-sampling knowledge. This large item pool included items from the reviewed scales and new items generated based on the results of a recent mixed methods synthesis of psychosocial factors affecting HPV test acceptability [24] and a systematic review of emotional responses to testing positive for HPV [25]. Items related to sociodemographics and health behaviors were also included.

All 781 items were compiled into an Excel (Microsoft Corporation) spreadsheet to be reviewed by the research team. A flowchart of the item sources is shown in Figure 2. Each item was reviewed individually over several research team meetings, marked as *retained* or *rejected*, and categorized into an appropriate section of the questionnaire (Figure 1). For instance, the item “The HPV test is safe” was categorized as part of *attitudes and beliefs about HPV testing* instead of *knowledge about HPV testing* because this item captures a belief that women may agree or disagree with, which may impact their intentions to engage in cervical cancer screening with the HPV test. Within each of the questionnaire sections, items were further mapped onto constructs from the HBM (eg, “if the HPV test showed I have HPV, it would be serious” in perceived seriousness) and TPB (eg, “my friends’ opinion about getting the HPV test would be important to me” in social cues) to ensure comprehensive coverage of these frameworks.

**Figure 1 figure1:**
[figure not shown]
Draft questionnaire structure. HPV: human papillomavirus; PAPM: Precaution Adoption Process Model.

**Figure 2 figure2:**
[figure not shown]
Flowchart of item sources.

At this stage, the focus was on the item’s underlying construct and not its wording. Reasons for rejecting items included the following: (1) duplicate of a factor already retained, (2) not applicable to Canadian context (eg, “There are resources in my community for low and no cost cervical cancer screenings” as Canada has a universal health care system [45]), (3) infrequent and isolated factor (eg, “I worry that tube contents may spoil or spill during transportation to doctor” [63]), and (4) not applicable to our project’s quantitative and survey methodology (eg, open-ended items such as “There are many warning signs and symptoms of cervical cancer. Please name as many as you can think of” [44]).

In total, of 781 items that were reviewed, 137 (17.5%) items were retained. Of these 137 items, 85 items were categorized for scale development: 14 for cervical cancer knowledge, 14 for HPV testing knowledge, 44 for attitudes and beliefs about HPV testing, and 13 for attitudes and beliefs about HPV self-sampling. These 85 items were reviewed and revised separately for clarity, consistency, and grade-8 reading level to account for different language and literacy levels. In addition, certain cervical cancer knowledge and HPV testing knowledge items were revised to achieve a balance of *true* and *false* items (ie, made negative or affirming by adding words such as *not*).

##### Assessing Preferences Using Best-Worst Scaling

To explore women’s preferences for their cervical cancer screening parameters (type of test, screening interval, and age of screening initiation), we designed questionnaire items according to the best-worst scaling (BWS) methodology [64]. Using this methodology, participants’ preferences were examined for different screening intervals (domain A) or various ages of screening initiation (domain B), while also considering multiple screening strategies (ie, Pap test, HPV test, HPV-Pap cotesting, and HPV self-sampling). In domain A, 3 screening intervals were included for assessment according to their applicability to HPV test–based screening implementation: 3 years (the most common interval in Canada for existing cytology-based programs [7]), 5 years (widely recommended for HPV test–based screening [20,65]), and 10 years (implemented for women aged ≥40 years in the Netherlands and considered for wider implementation [66]). In domain B, the following 3 ages of screening initiation were included: 21 years (the most common age of screening initiation in Canada for existing cytology-based programs [7]), 25 years (currently recommended age of screening initiation in several Canadian provinces and widely recommended in countries implementing HPV-based screening in the context of HPV vaccination; eg, the United Kingdom and Australia [7,20]), and 30 years (recommended age of screening initiation with primary HPV-based screening according to the United States Preventive Services Task Force guidelines [18,67]).

##### Informative Statements

Knowledge about HPV in the general population is generally very low [68,69], and knowledge about HPV testing and self-sampling is presumably low among Canadian women because such testing and sampling are not currently part of cervical cancer screening programs. Therefore, we sought to ensure that women had at least basic understanding of HPV testing and HPV self-sampling before examining their attitudes, beliefs, and intentions to screen with these tests. We designed 3 informative statements: one about HPV testing, one about self-sampling using HPV testing, and one comparing cervical cancer screening methods. The development of these statements was inspired by brochures from other countries where HPV-based primary screening is in the process of being implemented or already implemented (eg, the Netherlands, the United Kingdom, and Australia [70-72]). Each informative statement was at most 1 page in length and contained a mix of text, figures, and tables (refer to the example in Multimedia Appendix 1). All informative statements were included after the items that measure participants’ knowledge.

##### Questionnaire Revisions and Translation

A draft version of the questionnaire was circulated to our team of coinvestigators and collaborators (globally based researchers and public health decision makers with expertise in HPV research, cervical cancer screening, epidemiology, oncology, psychometrics, behavior change, and health psychology theory) for review of accuracy of content and feedback. Their suggestions were reviewed and used to refine our questionnaire further (ie, item wording, informative statement content, and questionnaire structure). Then, this version was translated into French by a specialized translation firm, Asiatis, and verified by a native French-speaking member of the research team ([name]).

#### Phase 1B: Questionnaire Validation

Given our objective of developing a comprehensible questionnaire, cognitive interviewing was used as a pretesting method to detect potential sources of errors in the question-answering process [73]. This method permits an assessment of the readability, understanding, and clarity of items to reveal potential differences between the intended meaning of the question from the researcher and the participants’ interpretations [74]. Participants were recruited to provide verbal feedback on their understanding and experience as they completed the questionnaire over Zoom (Zoom Video Communications) with 2 members of the research team being present. Participants read the items as if they were answering the questionnaire and were instructed and prompted to *think-aloud* and provide feedback and suggestions (eg, comment if they did not understand an item or were confused and explain how they reasoned and selected their response) [75]. Each interview lasted between 1 and 2 hours. Our team reviewed the participants’ comments after each interview session and made changes to the questionnaire iteratively to address the issues that arose.

The cognitive interviewing phase was completed when no new issues or feedback were raised by the participants. This process required a sample of 7 women, aged 21 to 70 years. Of the 7 interviews, 4 (57%) interviews were conducted in English and 3 (43%) were conducted in French. On the basis of the participants’ feedback, changes were made to the questionnaire to improve the clarity of items, informative statements, instructions, page formatting, and overall questionnaire structure and flow. Refer to Figure 3 for the final structure and item count.

**Figure 3 figure3:**
[figure not shown]
Study 1 questionnaire structure and item count. HPV: human papillomavirus; PAPM: Precaution Adoption Process Model.

#### Phase 1C: Data Collection and Psychometric Validation

##### Study Design

A cross-sectional web-based survey was administered from October 2021 to November 2021 to a national sample of Canadian women, aged 21 to 70 years, in English and French. Participants completed the questionnaire developed in phases 1A and 1B The survey design and preliminary results are reported according to Checklist for Reporting Results of Internet E-Surveys (CHERRIES; Multimedia Appendix 2) [76]. An electronic consent form describing the study investigators, study goals, procedure, expected survey length, and confidentiality was provided at the start of the survey. Then, the participants were asked whether they consented to taking part in the survey. By clicking on the icon that states they agree to participate, consent was implied, whereas if they declined, the survey was terminated. The information collected during the survey was completely anonymous.

##### Participants

The inclusion criteria were as follows: (1) born female; (2) aged between 21 years, which is the youngest age recommended to begin screening across provincial programs, and 70 years, which is the oldest age; (3) Canadian resident; and (4) intact cervix (eg, not having undergone hysterectomy). The exclusion criterion was having been diagnosed with cervical cancer previously. An oversampling quota was used to ensure that half of the sample was currently underscreened for cervical cancer (ie, >3 years since the previous Pap test or never screened) and the other half was adequately screened (ie, <3 years since the previous Pap test). Census-based quotas were used for primary language and province and territory of residence to reinforce sample representativeness.

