## Introduction

### Background

Cervical cancer is the fourth most common cancer in women and presents a significant risk to all people with a cervix [1-3]. In 2018, an estimated 570,000 women were newly diagnosed with cervical cancer worldwide, with 311,000 deaths from the disease [4]. In Canada, >1300 women are diagnosed with and >400 women die from cervical cancer each year [5]. Cytology testing using the Papanicolaou smear, commonly referred to as the Pap test, allows for the detection and subsequent treatment of precancerous lesions that may lead to cervical cancer. Canadian women have been widely screened for cervical cancer using the Pap test for >50 years [6]. There are guidelines in each province and territory that currently recommend screening every 1 to 3 years, starting at the age of 21 or 25 years [7], and most Canadian jurisdictions have organized screening programs [8].

Cervical cancer is caused by persistent infection with high-risk human papillomavirus (HPV) types [9]. The HPV test, which detects high-risk HPV DNA in cervical cells, has emerged as a significant improvement over cytology for cervical cancer screening. Compared with cytology-based screening, HPV-based screening has been shown to offer 60% to 70% higher protection against the development of cervical cancer [10,11]. The HPV test shows improved sensitivity, and negative test results have high negative predictive value, thus providing greater reassurance against cervical lesion development [12]. Furthermore, this allows for increased intervals between cervical screenings and reduced testing costs [12]. HPV testing also introduces the possibility for vaginal self-sampling by the patient. This is not possible with cytology, which requires cervical cell collection by a health care provider, a process that can be uncomfortable or invasive [13,14]. Meta-analyses have shown that self-sampling has similar test accuracy when compared with health care provider–administered sampling [15] and could increase uptake among those who are underscreened when provided as a screening option [15,16].

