### Screening Landscape in Canada

In Canada, provinces and territories are in different planning phases for HPV-based cervical cancer screening programs [7,27], and the nationwide introduction of HPV-based primary screening is a key priority of the recent Canadian Partnership Against Cancer (CPAC) Action Plan for the Elimination of Cervical Cancer [5]. Although cytology-based screening is well established in Canada, screening coverage has failed to reach the CPAC target of including ≥80% of women [28]. This suggests that innovative approaches are needed to reach those women who are underscreened (ie, longer than 3 years since their previous Pap test or never screened). Approximately 40% of women in Canada diagnosed with cervical cancer report either never having had a Pap test or not having had one in >3 years [29]. Underscreened women are often members of ethnic, linguistic, gender, and sexual minorities or have lower socioeconomic status [30-33]. In Canada, only 65% of recent female immigrants reported having a Pap test in the previous 3 years, and 26% of non-English or French speakers reported never having a Pap test [29]. In a study of cancer screening registries in Ontario, transgender patients were significantly less likely than cisgender patients to be screened for cervical cancer (56% vs 72%) [32], reflective of barriers faced by transgender and other gender-diverse people in seeking cervical cancer screening [2]. A study by Decker et al [34] comparing screening rates and outcomes between First Nations women and all other women in Manitoba suggested lower screening rates among First Nations women aged ≥40 years and significantly higher rates of cervical lesions and cancers in First Nations women overall. Targeted solutions must consider these factors. For underscreened women, the introduction of HPV self-sampling could be important for ensuring that cervical cancer screening is more accessible and acceptable [13-15,35,36]. A meta-analysis of 37 studies by Nelson et al [37] found that women who used and indicated acceptability of self-sampling for future screening did so because of its convenience, privacy, and ease of use. However, identified barriers include women’s lack of confidence in their ability to correctly collect the specimen, lack of confidence in the test result, and discomfort with the procedure [37,38].

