##### Screening History

Participants were asked when they last had a Pap test to assess their screening group: (1) within the past year, (2) within the past 1 to 3 years (adequately screened group), (3) >3 years ago, or (4) never (underscreened group). Then, the participants who reported receiving at least one previous Pap test were asked whether they had ever received an abnormal test result. In addition, given the study’s timing in the fall of 2021, participants who reported receiving a Pap test >3 years ago were asked whether the COVID-19 pandemic had prevented them from receiving a Pap test, as cervical cancer screening was paused in some provinces and territories during parts of the pandemic.

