#### Study Design

A cross-sectional web-based survey will be administered in summer of 2022 to a nationally representative sample of Canadian women, aged 21 to 70 years, in English and French. The study population and inclusion criteria will be the same as those in study 1. Oversampling will be used to ensure that half of the sample is adequately screened and the other half is underscreened. Additional quotas will be used for the following factors: age, household income, and rural or urban residence (considering low cervical screening rates in rural Canada [7]) based on census data from Statistics Canada. Data collection will be conducted by Dynata, following the same procedure as that in study 2.

The questionnaire will follow the same structure and include the same sections as the survey detailed in study 1. Of the knowledge, attitudes, and beliefs items used for scale development in study 1, only those items retained after extensive psychometric analyses will be used in the study 2 questionnaire as part of the resulting shorter, validated scales. In addition, 2 previously validated measures, the extended HPV General Knowledge and HPV Vaccine Knowledge scales, will be added [69], given the relevance of HPV and HPV vaccination in cervical cancer. The measurement of the outcome variables (intentions to screen using the HPV test and self-sampling) is informed by PAPM [81], a categorical, stage-based model of health decision-making. As a binary, *yes or no* outcome limits accuracy, using a multistage model provides a more precise, nuanced understanding of women’s decision-making process that acknowledges the unique barriers associated with movement between each stage toward engaging with the behavior [90].

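### Study 2 counts never-screened women below their own province's screening start age as underscreened

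*Protocol article*

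**What the plan says.** Screening status follows one national rule. The Introduction (Screening Landscape in Canada) describes underscreened women as "longer than 3 years since their previous Pap test or never screened". Participants repeats the rule for the quota: "currently underscreened for cervical cancer (ie, >3 years since the previous Pap test or never screened". Screening History shows how it is coded: "3) >3 years ago, or (4) never (underscreened group". None of the three places adds a condition on age or province.

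The lower age limit is set at the earliest start age in any program: "aged between 21 years, which is the youngest age recommended to begin screening across provincial programs". The article reports that start ages differ. Background says that guidelines "currently recommend screening every 1 to 3 years, starting at the age of 21 or 25 years", and the best-worst scaling section gives "25 years (currently recommended age of screening initiation in several Canadian provinces".

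For study 2, Study Design says "The study population and inclusion criteria will be the same as those in study 1", again with half of the sample underscreened, and adds census-based quotas for age, income and rural or urban residence. Data Analysis compares the two screening groups with t tests and chi-square tests (objective 1) and fits the multinomial models separately in each group (objective 2). Strengths and Limitations discusses recall of screening history and the effect of COVID-19 on group composition, and plans sensitivity analyses for the pandemic only.

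**The concern.** Read together, these statements put a never-tested 22-year-old in a start-at-25 province in the underscreened group, although she is doing what her program recommends. The Introduction presents underscreened women as those whom present programs fail to reach, and the Discussion promises targeted interventions from the group contrast. Women not yet due are not that target.

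The affected women are all aged 21 to 24, so the misclassification is linked to age. The objective 1 tests are unadjusted, so part of any difference between the groups may reflect youth rather than missed screening. One of the preference domains is the age of screening initiation, with 21, 25 and 30 years as the levels. Women waiting under a start-at-25 rule are placed on the underscreened side of exactly that comparison.

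Screening status carries both objectives of study 2, and it is also a recruitment quota. Once the quota has been filled under the present rule, reanalysis can remove the not-yet-due women but cannot replace them.

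**Working it through.** **The plan's own figures.** Study 2, Sample Size: N = 10 × 15 / 0.25 = 600; 600 / 0.40 = 1500 per group; 2 × 1500 = 3000 valid responses; 3000 / 0.82 = 3659, against the stated approximate 3650. These figures reproduce and are not in dispute.

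**Classification under the stated rule.** Take a woman who answers that she has never had a Pap test:

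| Age | Program start age | Due under her guideline? | Group in the plan |
|---|---|---|---|
| 21-24 | 21 | yes | underscreened |
| 21-24 | 25 | no | underscreened |
| 25 or over | 21 or 25 | yes | underscreened |

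The second row is the problem. It needs no outside information.

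**Size.** The documents do not give the inputs, so all of these are assumptions:
- a = share of women aged 21-24. With equal numbers at each age from 21 to 70, a = 4/50 = 0.08.
- q = share of these women in start-at-25 provinces: 0.2 to 0.8.
- v = share of those who were never screened: 0.5 to 0.8.
- u = share of all eligible women who are underscreened: 0.2 to 0.4.

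If the underscreened half is drawn at random from all underscreened women, the not-yet-due share is s = a × q × v / u.

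- Lowest: 0.08 × 0.2 × 0.5 / 0.4 = 0.02, or 30 of 1500.
- Middle, q = 0.5: 0.08 × 0.5 × 0.5 / 0.4 = 0.05 (75 of 1500), up to 0.08 × 0.5 × 0.8 / 0.3 = 0.107 (160 of 1500).
- Highest: 0.08 × 0.8 × 0.8 / 0.2 = 0.256, or 384 of 1500.

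The age quota limits the top of this range. If it is enforced on the whole sample, there are only 3000 × 0.08 = 240 women aged 21-24, so s cannot exceed 240 / 1500 = 16%. If it is enforced within each screening group, the limit is 1500 × 0.08 = 120 women, or 8%. The article does not say which applies.

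**Effect on objective 1.** Suppose that the not-yet-due women resemble adequately screened women. A standardized difference d then shrinks to d × (1 − s): 0.20 becomes 0.19 at s = 5% and 0.18 at s = 10%. For a true d = 0.10 with 1500 per group, two-sided power at the 5% level is Φ(0.10 × √750 − 1.96) = 78%. It falls to 74% at s = 5% (d = 0.095) and to 69% at s = 10% (d = 0.09). If these women differ from both groups, the bias could go either way.

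**The case against.** The strongest reply is that the definition is explicit and consistent. It is a transparent measure of time since the last test, and the article never equates underscreened with overdue under one's own provincial guideline. That stands as far as it goes: the plan does not contradict itself in the definition. But the article describes the group as women to be reached by new approaches, and it reports the differing start ages itself, so the label covers some women whom it was not meant to describe.

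A second reply is that the harm is small and partly handled: objective 2 uses multivariable models with sociodemographic factors, fitted within each group, and study 2 has age quotas. At the middle values the attenuation is indeed slight. However, adjustment within the underscreened group does not take the not-yet-due women out of it. The age quotas are not said to apply within screening group, and objective 1 is unadjusted.

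Some stronger readings are tempting, and the documents do not support them:
- A reader might infer that study 1 is affected too. There, screening status sets the recruitment quota only. The factor analyses use a random split, and no comparison by group is described.
- A reader might infer a firm percentage. The article also says that 21 is the most common start age among existing cytology programs, and it gives no population share for start-at-25 provinces.
- A reader might infer the same problem at older ages. The article calls 70 the oldest age across programs but states no earlier stop age.
- A reader might infer that a woman is underscreened only after more than three years within her program's ages. This would also remove never-screened women who are already eligible. With 3000 / 50 = 60 women per year of age and q = 0.5, the exposed pool, before applying the never-screened share, would be 60 × 3 × 0.5 + 60 × 7 × 0.5 = 300. The pool below the start age is 60 × 4 × 0.5 = 120.

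**Conclusion.** The point holds for study 2. The stated rule places guideline-compliant, never-screened women aged 21 to 24 in the underscreened quota, in the objective 1 contrast and in the underscreened-group models of objective 2. No planned sensitivity analysis covers them. That such women are misclassified is certain from the text; how many is not. The range of roughly 2% to 26%, with mid values of about 5% to 11%, rests entirely on assumed shares and equal numbers at each age, and a binding age quota would cut its upper end to 16% or 8%. At the middle values the dilution is modest; the link with age is the more awkward part. The sample-size arithmetic and the study 1 validation analyses are not affected. The change is worth making because it is cheap and concerns the main grouping variable.

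**What to change.** Before study 2 opens, derive a flag from age (a quota factor) and province or territory (already asked under Sociodemographics). A never-screened woman below her own province's start age is classed as not yet due. Never-screened women at or above that age stay underscreened. Apply a corresponding flag at older ages only where a program's guideline sets a stop age below 70.

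Preferably, instruct the panel firm not to count flagged women toward the underscreened quota. At minimum, keep the quota as it is, repeat the objective 1 contrasts and objective 2 models without the flagged women, and add the point to Strengths and Limitations.

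No new question is needed. Under the preferred option the cost is extra screen-outs. To reach 1500 remaining women at s = 2%, 5% or 10%, 1500 / (1 − s) = 1531, 1579 or 1667 women would have to be approached for that group, that is 31, 79 or 167 more. The minimum option costs one sensitivity analysis, but it leaves fewer than 1500 women in the reduced group.
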